
#### Sample Size

We assumed 85% clinical recovery in the group assigned to the full antibiotic course based on some studies [12,42-44]. Considering a power of 80%, a level of significance of 5%, one-sided noninferiority margin of 10%, as recommended by the guideline on the evaluation of medicinal products indicated for treatment of bacterial infections issued by the European Medicines Agency in 2022 [45], which gave a sample size of 402 patients. Assuming that the primary outcome could not be evaluated in 15% of patients, 474 patients needed to be included in the study (237 in the control group and 237 in the intervention group).

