We hypothesize that patients with ages ranging from 18 to 75 years who are allocated to the intervention group and are asked to discontinue antibiotic therapy as soon as they feel better and afebrile, their clinical stability criteria are normal (systolic blood pressure >90 mm Hg, axillary temperature <37 °C, respiratory rate <20 breaths/minute, and oxygen saturation >92%) and CRP falls within normal range will have a similar overall clinical efficacy at day 14 and will not present a higher reconsultation rate compared with those allocated to the control group. We expect a lower number of drug-associated adverse events in the intervention group.

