#### Assignment of Interventions: Allocation

##### Sequence Generation

Patients fulfilling the inclusion criteria will be asked to participate in the trial. All patients who agree to participate and provide signed informed consent will receive an increasing sequential patient number and be randomly assigned to one of the 2 treatment groups in a 1:1 ratio stratified per main diagnosis, one for acute rhinosinusitis and another one for lower RTI.

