### Statistical Methods

Statistical methods for primary and secondary outcomes: The characteristics of the study population will be described using frequencies for categorical variables and mean and SD for quantitative variables. To compare the clinical efficacy between the 2 strategies, we will analyze the difference in the proportion of recovered patients in each arm on day 14. Efficacy evaluation will be primarily based on intention-to-treat analysis in such a way that any event in any patient will be included in the group to which the patient was randomized, and per protocol analysis will be used as a secondary analysis. For all analyses, the level of significance will be *P*<.05.

Interim analyses: No interim analysis is planned.Methods for additional analyses (eg, subgroup analyses): We will conduct subgroup analyses of the primary outcome of participants with lower RTIs, and for acute rhinosinusitis.

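### The 402-patient sample size corresponds to a one-sided 2.5% noninferiority test, but the protocol article gives only 5% and P<.05 without sidedness and can be read as a one-sided 5% test

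*Protocol article*

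**What the plan says.** The protocol article describes a noninferiority trial with 1:1 allocation (Study Design), and its primary aim is noninferiority of day-14 clinical resolution (Objectives).

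- **Sample Size:** "We assumed 85% clinical recovery in the group assigned to the full antibiotic course". The error rates and margin follow: "Considering a power of 80%, a level of significance of 5%, one-sided noninferiority margin of 10" percent. The result is 402 patients, raised to 474 (237 per arm) because the primary outcome may not be evaluable in 15%.
- **Statistical Methods, primary comparison:** "we will analyze the difference in the proportion of recovered patients in each arm on day 14".
- **Statistical Methods, level:** "For all analyses, the level of significance will be" P<.05.
- **Sequence Generation:** allocation is in a "1:1 ratio stratified per main diagnosis, one for acute rhinosinusitis and another one for lower RTI".

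No section says whether the 5% or the P<.05 is one-sided or two-sided, and 2.5% appears nowhere.

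**The concern.** In a noninferiority trial the level must be given together with its sidedness, because 5% two-sided and 5% one-sided are different tests: the lower limit of a 95% interval in one case, of a 90% interval in the other. Here the word one-sided stands directly after the 5% and before the margin. Since it is normally a test and not a margin that is called one-sided, a reader can easily take the sentence to mean a one-sided 5% test. The later P<.05, applied to all analyses including the primary one, does not settle the matter.

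At stake is the error rate of the trial's primary claim. An analyst working from this text could choose either level. The Blinding section says it is difficult to keep outcome assessors and data analysts unaware of allocation, so a choice left open until the analysis would be hard to defend as independent of the data.

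**Working it through.** **Inputs**
- Control resolution 85%, power 80%, margin 10 points, 402 evaluable, 15% not evaluable, 474 enrolled: Sample Size.
- Allocation 1:1: Study Design.
- Intervention resolution 85%: my assumption. The article gives no figure, but the Objectives section expects that the intervention group "will have a similar overall clinical efficacy at day 14".

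**Formula** (noninferiority of two proportions, unpooled variance, true difference zero)

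n per arm = (z_α + z_β)² × 2 × 0.85 × 0.15 / 0.10², with z_β = 0.842

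**Reproducing the article's figure, one-sided 2.5%**
- (1.960 + 0.842)² = 7.849, and 7.849 × 0.255 / 0.01 = 200.1, so 201 per arm and 402 in total. This is an exact match.
- 402 / 0.85 = 472.9, so 473, or 474 with equal arms. This also matches.

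**The same formula, one-sided 5%**
- (1.645 + 0.842)² = 6.183, and 6.183 × 0.255 / 0.01 = 157.7, so 158 per arm and 316 in total.
- 316 / 0.85 = 371.8, so 372 enrolled.

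**Other formulas at one-sided 5% and 80% power.** Restricted maximum-likelihood (Farrington-Manning) variance gives 326, and a continuity correction gives 356. Treating the problem as a test of 85% against 75% gives 390 (unpooled), 394 (pooled) or 434 (with continuity correction). None gives 402. The figures 390 and 394 come within 3%, but they are not the usual noninferiority calculation with equal true rates.

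**Power with 201 per arm**
- Standard error at 85% in both arms: √(0.255 / 201) = 0.0356, and 0.10 / 0.0356 = 2.808.
- One-sided 2.5%: Φ(2.808 − 1.960) = Φ(0.848) = 80.2%.
- One-sided 5%: Φ(2.808 − 1.645) = Φ(1.163) = 87.8%.

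**False noninferiority risk.** This is an exact binomial calculation with 201 per arm, Wald limits, and true resolution of 75% (intervention) against 85% (control). The lower limit exceeds −10 points with probability 2.5% for a 95% interval and 5.2% for a 90% interval.

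**Largest observed deficit that still passes** (same standard error)
- 95% interval: 10 − 1.960 × 3.56 = about 3.0 points.
- 90% interval: 10 − 1.645 × 3.56 = about 4.1 points.

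An observed deficit between these two values would fail under one reading and succeed under the other.

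**Stratifying by diagnosis** (assuming equal strata and an overall rate of 85%). The unstratified variance term is 0.85 × 0.15 = 0.1275.
- Stratum rates 90% and 80%: (0.09 + 0.16) / 2 = 0.125, which is 2% less.
- Stratum rates 95% and 75%: (0.0475 + 0.1875) / 2 = 0.1175, which is 8% less.

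**The case against.** The strongest reply is that nothing is miscalculated. Grammatically, one-sided qualifies the margin and not the 5%. An unqualified P<.05 is ordinarily two-sided, and a two-sided 5% level gives exactly 402 and 474. On that reading the two sections agree and no error rate is doubled. This stands: the article does not state a one-sided 5% level, and the sample size is not wrong.

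Three stronger inferences are tempting, and the documents do not support them.

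- *That the trial will run at double the intended error rate.* This follows only if P<.05 is applied one-sided to the noninferiority test, which the article does not say.
- *That a nonsignificant difference will be taken as noninferiority.* The design, the primary aim and the margin are all stated in noninferiority terms, and the difference in proportions is the scale of that margin. No such analysis is proposed.
- *That the missing confidence-limit rule and the unstratified comparison are errors in themselves.* An article may leave both to the full protocol or analysis plan, which are not shown. Ignoring a stratification factor generally makes the test somewhat conservative, so it does not add to the false noninferiority risk. Diagnosis is also used in the planned subgroup analyses.

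The reply does not remove the ambiguity. The article fixes a level in two places, and in neither does it identify the test that 402 was computed for.

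**Conclusion.** The point holds as an ambiguity in the stated level, not as a sample-size error. Of the calculations tried, only the standard noninferiority formula at one-sided 2.5% returns 402; at one-sided 5% it returns 316. The text permits the one-sided 5% reading. If that reading were applied to 402 evaluable patients, the false noninferiority risk would be about 5% instead of 2.5%, and power about 88% instead of 80%. If the 5% is two-sided, the risk is 2.5% and the design is consistent.

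These figures assume 85% true resolution in both arms for power, 75% against 85% for the error risk, 201 evaluable per arm, and Wald limits. The consequence is conditional, but it concerns the primary conclusion, so the level should be settled before any outcome data are seen.

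**What to change.** 1. **Sample Size:** state the level as one-sided 2.5% (equivalently 5% two-sided). The figures 402 and 474 stay as they are.
2. **Statistical Methods:** replace the blanket P<.05 for the primary outcome with an explicit rule: noninferiority is concluded if the lower limit of the two-sided 95% confidence interval for the difference in day-14 resolution (intervention minus control) lies above −10 percentage points. Keep two-sided P<.05 for the secondary comparisons.
3. **Minor improvement:** stratify that interval by diagnosis, the randomization factor, for example with Mantel-Haenszel weights or a stratified Miettinen-Nurminen interval. Under the assumptions shown, this lowers the variance by about 2% to 8%.

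The cost is a few words in each of two sections. No patients are added, and the margin and design do not change. If the sponsor did intend one-sided 5%, the sample-size statement would have to be corrected instead, because 402 then gives about 88% power and not 80%.

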#### Recruitment

A total of 474 eligible patients will be enrolled by doctors in 25 primary care centers throughout Spain. Centers with a minimum of 3 health care professionals willing to participate in the trial will be invited to join the study. The study is planned to run from October 2025 to April 2027, including 2 winter periods (last patient recruited in March 2027). A tight follow-up on the process and different strategies will be implemented, and if needed (1) other professionals in the existing centers will be invited to participate in the study; (2) we can extend the recruitment period by an additional 2 months, until May 2027 (last follow-up in June 2027); or (3) other sites will be opened to increase the candidates to enter the study. Monthly meetings will be held with the coordinators at the different centers to maintain recruitment and enrollment activity during the inclusion period.

#### Assignment of Interventions: Allocation

##### Sequence Generation

Patients fulfilling the inclusion criteria will be asked to participate in the trial. All patients who agree to participate and provide signed informed consent will receive an increasing sequential patient number and be randomly assigned to one of the 2 treatment groups in a 1:1 ratio stratified per main diagnosis, one for acute rhinosinusitis and another one for lower RTI.

##### Concealment Mechanism

Since this study is open-label to patients and investigators, randomization will be based on investigator-blinded blocks of randomly varying size to protect against the potential predictability of treatment assignments. Blocks will be small to decrease the potential for mid-block inequality.

##### Implementation

The allocation sequences will be prepared by one remote independent researcher who is available to generate more allocation sequences.

#### Assignment of Interventions: Blinding

Owing to the type of intervention, participants and GPs are not blinded to group allocation. It is also difficult for the principal investigator and members of the research team involved in obtaining and analyzing the data (outcome assessors and data analysts) to be blinded to group allocation, as patients allocated to the intervention group have more visits scheduled.

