### Outcomes

#### Primary Efficacy Endpoint

The primary outcome is the percentage of patients achieving clinical resolution, defined as the disappearance of fever and either the disappearance or improvement in overall condition, such that no additional antimicrobial treatment is necessary. Any other clinical outcome that does not meet the definition is considered treatment failure. The evaluation will take place on day 14 via a phone call and will always be conducted by a doctor from the team of physicians participating in the study.

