**Figure 1 figure1:**
[figure not shown]
Study flowchart of the clinical trial. COPD: chronic obstructive pulmonary disease; CRP: C-reactive protein; RTI: respiratory tract infection; SOFA: sequential organ failure assessment.

**Table 3 table3:** Ascertainment of visits for the clinical trial.

	V1^a^	V2^a^	V3^a^	V4^a^	V5^a^	V6^a^
	Face-to-face visit		Phone call			
	Day 0 (baseline visit)	From day 1^b^ (interv)	Day 3 (±1 day)	Day 7	Day 14	Day 28
Medical history	✓	✓				
Standard physical examination	✓	✓				
Eligibility criteria	✓					
Informed consent	✓					
Prescription of the antibiotic	✓					
Randomization	✓					
EQ-5D-5L questionnaire	✓				✓	✓
Hand-out of the symptom diary	✓					
CRP^c^ rapid testing		✓				
Decision to stop antibiotic course		✓				
Collection of the symptom diary		✓			✓	
Assessment of the clinical efficacy			✓	✓	✓	
Assessment of the drug adherence		✓	✓	✓	✓	
Monitoring of adverse events			✓	✓	✓	✓
Complications, re-attendance			✓	✓	✓	✓

^a^Visits 1-6.

^b^As soon as the patient feels better, only for patients in the intervention group.

^c^CRP: C-reactive protein.

Patient data will be collected at 4 specific time points for patients assigned to the control group and 5 for those allocated to the intervention:

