Day 0 (inclusion date at the center): Patients meeting the inclusion criteria will be invited to join the study by their GP. After obtaining informed consent, patients will be randomized into either the control group (receiving a full course of β-lactam therapy for at least 7 days) or the intervention group (instructed to return for assessment upon feeling better and being afebrile). The GPs will complete a case report form on day 0 (inclusion day), recording details such as age, inclusion and exclusion criteria, symptoms, date of symptom onset, comorbidities, concomitant medication, quality-of-life questionnaire (EQ-5D-5L instrument), randomization, assigned group, and details of the antibiotic administered. Patients will also be provided with a symptom diary (web-based or paper-based)From day 1 until the last day of the antibiotic regimen duration (at the center, only for patients assigned to the intervention group): For patients assigned to the intervention, they will be asked to return to the center for clinical reassessment and CRP rapid testing by the professional. Each center will organize ways to make it easy for patients to reach out and schedule an appointment as soon as they feel better (eg, phone number and web-based page). To decide whether to discontinue the antibiotic course when the patient reports feeling better during the consultation, three types of assessment are needed: (1) overall improvement in the patient’s symptoms; (2) signal signs are in normal range (temperature <37 °C; blood pressure >90/60 mm Hg; pulse < 100 beats/minute; respiratory rate <20 breaths/minute, and oxygen saturation >92%), and (3) CRP value is lower than the prespecified values depending on the day of the visit. All this information will be recorded in the electronic case report form (e-CRF; Table 1)Day 3±1 (phone call, only for patients assigned to the intervention group): A reminder phone call for all patients assigned to the intervention group will be made on this day. They will be asked how they feel and reminded to reach out to the center as soon as they feel better for a discontinuation assessmentDay 7 (phone call): An early clinical efficacy outcome will be assessed during this call, including the clinical progression of signs and symptoms, treatment adherence, adverse reactions, any complications, reattendance visits, changes to the assigned treatment or concomitant medication, and the use of antibiotics other than the study drugDay 14 (phone call): The main clinical efficacy outcome and some secondary outcomes, including clinical progression of signs and symptoms, compliance with the study treatment, EQ-5D-5L instrument, adverse reactions, any complications, reattendance visits, changes in the assigned treatment or concomitant medication, including the use of antibiotics other than the study medication, will be assessed. Patients will be asked to return their diariesDay 28 (phone call): Patients will be contacted for information on the number of reconsultations, complications, and the quality-of-life (EQ-5D-5L) instrument

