### Methods in Analysis to Handle Protocol Nonadherence and Any Statistical Methods to Handle Missing Data

Analyses will be performed as intention to treat (pragmatic trial) and also per protocol. The primary analysis population will comprise all participants, irrespective of follow-up.

Data will be examined for missing values and outliers. Measures of central tendency and dispersion for continuous study parameters will be portrayed. Extreme or unexpected values will be examined individually for authenticity, and data discrepancies addressed where appropriate.

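### The reason given for not blinding data analysts, extra intervention-arm visits, does not apply to the day-14 primary analysis, which could be cleaned, locked and run on a minimal file with coded arms

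*Protocol article*

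**What the plan says.** The protocol article's section on blinding states that participants and GPs know the allocation. It then says blinding is also difficult for the principal investigator and for the team members collecting or "analyzing the data (outcome assessors and data analysts) to be blinded to group allocation, as patients allocated to the intervention group have more visits scheduled". This is the only reason offered, and it covers outcome assessors and data analysts together. The article describes no coded file and no masked cleaning or analysis.

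On the primary outcome, the Primary Efficacy Endpoint section says: "The evaluation will take place on day 14 via a phone call and will always be conducted by a doctor from the team of physicians" taking part in the study. The Statistical Methods section says that "we will analyze the difference in the proportion of recovered patients in each arm on day 14", primarily by intention to treat, and that "per protocol analysis will be used as a secondary analysis".

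Two contacts are specific to one arm. One is the centre visit, which Table 3 footnotes as "As soon as the patient feels better, only for patients in the intervention group". The other is the reminder call, listed in the Participant Timeline as "Day 3±1 (phone call, only for patients assigned to the intervention group").

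On cleaning, the section on nonadherence and missing data says: "Extreme or unexpected values will be examined individually for authenticity, and data discrepancies addressed where appropriate". The same section keeps every participant in the primary analysis population whether or not they were followed up. The Sample Size section expects no evaluable primary outcome in 15% of patients.

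**The concern.** The protocol takes a position on analyst blinding and defends it with a reason, so this is not a detail merely left to a statistical analysis plan. The reason does not fit the task it is meant to excuse. Extra visits can reveal the arm to someone who reads visit-level records. They reveal nothing to someone given a file without visits.

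Patients, GPs and outcome assessors are already open, and the outcome includes a judgement that the patient's overall condition has improved. Analyst-level cleaning and the primary analysis are steps that can still be masked. What is at stake is discretion over day-14 records: how a discrepant result is settled, and how patients without a result are counted. If such choices are made with the arm known, a noninferiority result near its margin can be influenced, or can be suspected of having been.

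**Working it through.** **Step 1. Does the stated reason reach the primary analysis?** The items that the primary analysis could need are:

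| Item | Source in the protocol article | Present in both arms? |
|---|---|---|
| Day-14 resolution (yes/no) | Primary Efficacy Endpoint; Participant Timeline, day 14 | Yes, same call |
| Diagnosis stratum | Sequence Generation | Yes, set at randomisation |
| Arm label | Randomisation at day 0 | Yes, can be coded A/B |
| Centre visit and CRP | Table 3 | Intervention only; not needed |
| Day-3 call | Participant Timeline | Intervention only; not needed |

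The visits that differ by arm are not inputs to the day-14 difference in proportions.

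**Step 2. Which other fields would reveal the arm?** The diary, day-7 and day-14 forms are used in both arms, but their content is not neutral. The diary records the antibiotic doses taken each day. The short form for unreturned diaries asks about antibiotic use after a doctor had stopped the course. The day-7 and day-14 calls cover adherence or compliance and treatment changes. Early stopping is the intervention, so these fields would disclose the arm for many patients. A file is masked only if they are removed as well.

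**Step 3. Reproduce the plan's sample size.** Inputs from the Sample Size section are 85% recovery (taken as equal in both arms), a 10-point margin, 80% power and 5% significance. Read as a two-sided 5% level (2.5% one-sided):

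n per arm = (1.960 + 0.842)² × 2 × 0.85 × 0.15 / 0.10² ≈ 200.2, rounded up to 201, so 402 in total.

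201 / 0.85 = 236.5, rounded up to 237 per arm, so 474 in total. Both stated figures reproduce. With a one-sided 5% level the result would be 158 per arm (316), which does not match.

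**Step 4. Weight of one record.** 1/201 = 0.005, or 0.5 percentage points per reclassified patient.

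**Step 5. A borderline illustration.** Assumptions: 171/201 (85.1%) resolved in control, and a Wald two-sided 95% interval, with lower limit = d − 1.96 × √[p_C(1−p_C)/201 + p_T(1−p_T)/201].

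- Intervention 166/201: d = −2.5 points, lower limit −9.7, margin met.
- Intervention 165/201: d = −3.0 points, lower limit −10.2, margin missed.

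One record can decide a result that happens to fall there.

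**Step 6. Bounds from missing outcomes.** Assume 237 − 201 = 36 missing per arm and 171 observed successes in each arm.

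- All missing counted as failures in both arms: difference 0, lower limit −8.1.
- All missing counted as successes in both arms: difference 0, lower limit −6.0.
- Opposite handling in the two arms: difference ±36/237 = ±15.2 points.

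The last line is an arithmetical extreme that no reasonable plan would adopt. Steps 4 to 6 show how sensitive the result is to such decisions. They do not say how large any bias would be.

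**The case against.** The case against has force on several points.

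- **The wording is mild.** The section calls blinding difficult. A reader might infer that analysts will definitely work with open labels, but the text does not say so. What can be said is that it commits to no masking and gives a reason that does not cover the primary analysis. Coded exports and lock order often sit in an analysis or data management plan. That would answer a complaint about silence, but not one about a stated rationale.
- **Most of the data are not arm-neutral.** A reader might infer that only the centre-visit and day-3 forms disclose the arm, so that all diary and follow-up data could be exported masked. Step 2 shows otherwise. Only a minimal file works.
- **The cleaning text is mainly about other variables.** The cross-check of calls against clinical records is listed for secondary outcomes, not for day-14 resolution. The sentence on extreme values follows one on continuous parameters, and a yes/no outcome has no outliers. Only the general clause on discrepancies can reach the primary outcome, together with the handling of missing results.
- **No bias has been sized.** One could say that six records settled in one direction would shift the difference by 6/201 = 3.0 points. Nothing in the document suggests that this number, or any number, would be settled that way.
- **The main exposure lies elsewhere.** A study doctor who knows the arm judges the outcome by phone, and the Limitations section acknowledges that masking is not used. Coding the analyst's file does not change that. Queries answered by the centres also remain unblinded.

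These points narrow the concern but do not remove it. The stated reason still fails for the primary-outcome file.

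**Conclusion.** The point holds in a limited form. More scheduled visits do not prevent masked cleaning and analysis of the primary outcome, because that analysis uses nothing from those visits. The exposure is confined to analyst-level decisions on discrepant or missing day-14 results. Each reclassified patient is worth 0.5 points with 201 evaluable per arm, against a 10-point margin. The borderline illustration rests on an assumed control result of 171/201 and a Wald interval. The missing-data bounds rest on 36 missing per arm.

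The importance is minor. The sample size is unaffected, intention-to-treat analysis of a simple difference leaves an analyst little room, and the larger bias from open assessment would remain. The change is still worth making because it is cheap and only needs to be in place before cleaning and lock.

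**What to change.** Amend the Blinding section to treat data analysts separately from outcome assessors, and state that:

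1. A minimal primary-outcome file is exported from REDCap with study code, diagnosis stratum, arm coded A/B and day-14 resolution. The assigned group recorded at day 0 is replaced by the code.
2. Centre-visit, day-3, CRP, diary antibiotic-dose, antibiotic-duration, adherence and treatment-change fields are withheld until the code is released.
3. Analyst-level decisions on discrepant and missing day-14 results are made on this file. It is then locked, and the primary intention-to-treat analysis is run. The interval for A minus B can be computed masked, and its direction is read against the margin once the code is opened.
4. Per-protocol, antibiotic-duration and stop-criteria analyses follow release of the code, because they need the withheld fields.
5. A code holder is named. The Implementation section says "The allocation sequences will be prepared by one remote independent researcher". That person is a natural candidate, but the stated role covers sequence generation only and would have to be extended.

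The cost is one additional export, one additional locking step and the code holder's time. Enrolment, visits and patient care do not change. The text should also say plainly that this protects only analyst-level handling, and that the day-14 phone assessment remains unblinded.
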